#### Plans for collection, laboratory evaluation, and storage of biological specimens for genetic or molecular analysis in this trial/future use {33}

N/A; biological specimens will not be collected in this study.

## Statistical methods

### Statistical methods for primary and secondary outcomes {20a}

Given the 2-phase RCT design, group comparisons for sleep outcomes will be assessed at phase 1 post-treatment. We will compare insomnia symptoms (primary outcome), sleep quality, and sleep patterns and their corresponding changes from baseline to phase 1 post-treatment between CBT-I and Sleep EDU using the Student *t*-tests or chi-squared tests. Baseline demographic and pre-treatment variables are expected to be balanced across treatment conditions by randomization but will be checked. We will conduct covariate-adjusted regression analysis on the outcomes: linear regression models on continuous outcomes and logistic regression models on binary outcomes, with a priori identified biological covariates (age, sex), sociodemographic variables (race, ethnicity), and baseline outcome values. The predictor of interest is the treatment condition indicator. All regression models will be carefully assessed using residual analysis and goodness-of-fit statistics (deviance, likelihood ratio, information criteria, etc.). The primary hypotheses will be tested using the Wald test on the coefficient estimates of treatment condition indicator.

Group comparisons for headache outcomes and emotional and health outcomes will be assessed at phase 2 post-treatment and 6-month follow-up. Similar analyses as outlined for phase 1 outcomes above will be applied for cross-sectional analyses of post-treatment phase 2 outcomes. Longitudinal data analysis will examine the sleep and headache outcome variables assessed at all 4 time points (baseline, phase 1 post-treatment, phase 2 post-treatment, 6-month follow-up). All regression models will have the following form: outcome ~ group + time + time × group + confounders. We will model time as a discrete variable. The differences in changes from baseline in outcomes between the treatment groups will be assessed by testing the significance of coefficients for the time-by-group interaction terms using the Wald test (individual) and likelihood ratio test (overall). To account for clustering due to repeated assessments within individuals, we will use linear and generalized linear mixed effects regression models.

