## Introduction

### Background and rationale {6a}

Migraine is a major pediatric health problem impacting 10–12% of adolescents [1, 2]. Poor sleep is a common comorbidity, with 60–70% of youth reporting elevated insomnia symptoms [3, 4]. Recent studies suggest 30% of adolescents with migraine meet the diagnostic criteria for insomnia [5]. Insomnia is associated with poor outcomes for youth with migraine including greater headache-related disability, more frequent headaches, higher pain intensity, greater depression/anxiety, and greater health service use [4, 6, 7]. There is robust evidence showing the efficacy of psychological treatment for improving headache-related disability and pain in youth with migraine [8, 9]. However, improvements in sleep have been inconsistent [10, 11]. In fact, our preliminary data show that poor baseline sleep is a risk factor for youth to achieve less improvement in pain outcomes with cognitive-behavioral pain treatment (CBT-Pain) [11].

To cope with migraine, youth commonly engage in maladaptive sleep behaviors (e.g., caffeine overuse, napping, excessive time in bed) that can increase negative cognitions about sleep, disrupt sleep physiology, and lead to a vicious cycle of insomnia symptoms that, in turn, increase the propensity for migraine [12, 13]. We propose that insomnia is a critical treatment target for youth with migraine and that treatment of insomnia could have positive effects on headaches by increasing healthy sleep behaviors and reducing anxiety at bedtime (see Fig. 1 for an illustration of this conceptual model).

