### Trial design {8}

In this two-phase randomized controlled trial with two parallel study arms, we will assess the superiority of CBT-I over Sleep EDU and the superiority of the combined effect of CBT-I + CBT-Pain over Sleep EDU + CBT-Pain. The patient allocation ratio is 1:1. Outcome assessments are administered at baseline, phase 1 post-treatment, phase 2 post-treatment, and 6-month follow-up. See Fig. 2 for an illustration of the trial design and study flow.

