### Sample size {14}

Sample size estimates were based on our team’s preliminary data for CBT-I intervention for adolescents [14, 15], Internet-delivered CBT-I for adults [23, 25], our WebMAP trials [16, 17], and other trials of CBT-Pain in youth with headache or migraine [8, 37, 38]. Based on these preliminary data, power analyses indicated that 77 subjects per group would provide 80% power to detect a moderate effect size (Cohen’s *d* = 0.45) on the primary sleep outcome of insomnia symptoms (ISI [27]) and the primary headache outcome of headache-related disability (CALI-9 [31]). Attrition in our prior web-based trials has been less than 10% [16, 17]. With attrition conservatively estimated at 15%, we expect to enroll 180 subjects to achieve a final sample size of 154 subjects.

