#### Implementation {16c}

After completing informed consent, assent, and the pre-treatment assessment, the study staff will use the REDCap randomization framework to allocate the participant to one of the study arms. Different study staff will generate the allocation sequence, conduct participant enrollment, and assign participants to interventions.

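### The cross-sectional phase 2 CALI-9 model leaves out baseline insomnia severity, a predictor that the protocol's own rationale points to; adding it is a small gain in precision at almost no cost

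*Protocol article*

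**What the plan says.** - **Covariates.** Statistical methods {20a} plans linear or logistic regression "with a priori identified biological covariates (age, sex), sociodemographic variables (race, ethnicity), and baseline outcome values". The primary hypotheses are tested by a Wald test on the treatment coefficient.
- **Phase 2.** The same section applies similar analyses to the cross-sectional phase 2 outcomes. For CALI-9 the baseline outcome value is most naturally baseline CALI-9. No baseline sleep measure is listed.
- **Longitudinal model.** It contains group, time, their interaction and confounders. The confounders are not named.
- **Rationale.** Background and rationale {6a} cites the team's preliminary data that "poor baseline sleep is a risk factor for youth to achieve less improvement in pain outcomes with cognitive-behavioral pain treatment (CBT-Pain"). It also links insomnia with greater headache disability and more frequent headaches.
- **Availability.** Outcomes {12} measures the ISI at baseline. Implementation {16c} randomizes "After completing informed consent, assent, and the pre-treatment assessment".
- **Allocation.** Sequence generation {16a} describes varying block sizes and no stratification.
- **Power.** Sample size {14}: "77 subjects per group would provide 80% power to detect a moderate effect size", with Cohen's d of 0.45 for both ISI and CALI-9.

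**The concern.** The trial exists because sleep is thought to affect how adolescents respond to CBT-Pain. Everyone receives CBT-Pain in phase 2, so a baseline measure of sleep trouble is a natural prognostic variable for the phase 2 primary outcome. The covariate list does not follow from that rationale. It includes race and ethnicity, for which the article offers no evidence of prediction, and omits the one baseline characteristic that the Background singles out.

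Two things are at stake, both limited. First, variance in CALI-9 that baseline ISI could explain stays in the residual and widens the confidence interval. Second, with no stratification on insomnia severity, a chance difference between arms can be corrected only in the analysis. The text says that baseline variables will be checked for balance. A covariate added after such a check, or after unblinding, is open to the charge of being chosen from the data, so it should be named in advance.

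**Working it through.** **Inputs from the protocol:** 77 per arm, d = 0.45, 80% power, 1:1 allocation, 15% attrition, 180 enrolled for 154 analysed.

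**Assumptions, not in the documents:** two-sided 5% level; partial correlation r of baseline ISI with phase 2 CALI-9, given the other covariates, of 0.1 to 0.3; correlation ρ of baseline with phase 2 CALI-9 of 0.5, with 0 and 0.3 for comparison.

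**1. The plan's own figure.** n per arm = 2(1.960 + 0.842)²/0.45² = 77.5 (78.5 with the exact t-test). With 77 per arm, power is 79.2% by the noncentral t and 79.7% by the normal approximation. For attrition, 154/0.85 = 181 and 180 × 0.85 = 153. The stated 77 and 180 reproduce within rounding. The calculation takes no visible credit for covariate adjustment.

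**2. Effect of adding baseline ISI.** With the raw SD set to 1, the residual SD is s = √[(1 − ρ²)(1 − r²)]. The noncentrality is (0.45/s) × √(77/2), and power comes from the noncentral t with 152 degrees of freedom. The equivalent number of extra participants is 154/(1 − r²) − 154.

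For example, with ρ = 0.5 and r = 0.2, s = √(0.75 × 0.96) = 0.849. The noncentrality is 0.45/0.849 × 6.205 = 3.29, and power is 90.5%.

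| r | partial R² | extra participants on 154 | power, ρ = 0.5 | power, ρ = 0.3 | power, ρ = 0 |
|---|---|---|---|---|---|
| 0 (ISI omitted) | 0% | 0 | 89.3% | 82.9% | 79.2% |
| 0.1 | 1% | 1.6 | 89.6% | 83.2% | 79.6% |
| 0.2 | 4% | 6.4 | 90.5% | 84.3% | 80.8% |
| 0.3 | 9% | 15.2 | 91.9% | 86.2% | 82.9% |

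With ρ = 0.5 the gains are 0.3, 1.2 and 2.6 points. With ρ = 0 they are 0.4, 1.6 and 3.6 points. The planned model already contains baseline CALI-9, so the ρ = 0 column applies only if d = 0.45 was meant on the residual scale, which the section does not say. Taking six degrees of freedom for covariates lowers these powers by only about 0.02 points.

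**3. Chance imbalance.** With 77 per arm, the standardized difference between arms in the part of ISI unrelated to the other covariates has SD √(2/77) = 0.161, with 95% limits of ±0.316. With ρ = 0.5 (residual SD 0.866), a difference at the limit moves the CALI-9 estimate by 0.316 × r × 0.866. This is 0.027, 0.055 or 0.082 SD for r = 0.1, 0.2 or 0.3, or 6%, 12% or 18% of the target effect of 0.45. Adjustment removes this shift. It is the same variance as in step 2, seen in a single trial, and not a further loss.

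**The case against.** The strongest reply is that nothing in the list is wrong. Baseline CALI-9 is normally the best single predictor and is included. Randomization protects the estimate. One more covariate is a preference. Most of this stands, and it fixes the size of the point.

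Four stronger readings are tempting, and the documents do not support them:

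- *The phase 2 result would be biased or underpowered.* Neither follows. The estimate is unbiased over randomizations, and the stated sample size claims nothing from adjustment.
- *The protocol has shown that ISI predicts CALI-9.* The Background speaks of poor baseline sleep and pain outcomes. It names neither instrument and gives no coefficient. Choosing the ISI is an inference, a reasonable one because it is the trial's primary insomnia measure. Eligibility {10} admits only adolescents who meet insomnia criteria, which may narrow the spread of ISI, and baseline CALI-9 may absorb part of the association. Low values of r are plausible.
- *Baseline headache days should be added too.* No passage indicates that they predict CALI-9 beyond baseline CALI-9, and both come from the same 14-day diary.
- *The longitudinal model omits insomnia as well.* Its confounders are unnamed, so it neither includes nor excludes ISI. The omission is definite only for the cross-sectional model.

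It may also be said that ISI could predict less well in the arm that has already had CBT-I. That is possible, and a common slope need not be exactly true. With equal allocation ("The patient allocation ratio is 1:1"), however, a common-slope adjustment does not lose precision in large samples. An unequal slope therefore reduces the gain and does not reverse it.

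**Conclusion.** The point holds as a missed efficiency gain in one stated model. The a priori covariates for the cross-sectional phase 2 CALI-9 analysis omit baseline insomnia severity, although the protocol's rationale identifies poor baseline sleep as a predictor of response to the treatment that both arms receive.

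The size is modest and rests on an assumed partial correlation. At 0.1 to 0.3 it is worth about 2 to 15 participants on 154, or 0.3 to 2.6 power points with baseline CALI-9 in the model at an assumed correlation of 0.5. Adjustment also protects against a chance imbalance in insomnia severity. This is not an error of validity or of sample size, and it gives no reason to remove race or ethnicity.

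**What to change.** Before unblinding, state in the analysis plan that the baseline ISI total enters as a continuous a priori covariate in the phase 2 models for CALI-9, headache frequency and headache pain intensity, beside the covariates already listed. Name it also among the confounders of the longitudinal model for these outcomes. There it should enter with its interaction with time, because a main effect alone largely cancels from contrasts of change from baseline.

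The cost is one or two sentences. It takes one degree of freedom out of about 150 in the cross-sectional model and a few more in the longitudinal one. No new data are needed, and neither the sample size nor the other covariates change. If the analysis plan already contains this, only the published description needs to be aligned.

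### The longitudinal model gives baseline a free group effect, so its interaction test loses the precision of baseline adjustment, chiefly for CALI-9 and the other headache outcomes

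*Protocol article*

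**What the plan says.** All of the analysis text is in the protocol article, Statistical methods for primary and secondary outcomes {20a}. It describes three layers.

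- **Unadjusted comparisons.** t-tests (or chi-squared tests) on outcomes and on their changes from baseline.
- **Cross-sectional regression at one time point.** The covariates are age, sex, "sociodemographic variables (race, ethnicity), and baseline outcome values". The primary hypotheses are tied to the Wald test on the treatment indicator in this regression. Analyses of the same kind are then extended to phase 2 post-treatment.
- **Mixed models over time.** "Longitudinal data analysis will examine the sleep and headache outcome variables assessed at all 4 time points", baseline being the first of the four. The form is "All regression models will have the following form: outcome ~ group + time + time × group + confounders", with time categorical. Differences in change from baseline are tested through the interaction terms, singly by Wald tests and jointly by a likelihood ratio test.

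The same section says that headache outcomes will be compared at phase 2 post-treatment and at 6 months. Outcomes {12} defines the CALI-9 primary outcome as change from baseline to all three later assessments. Sample size {14} states that "power analyses indicated that 77 subjects per group would provide 80% power" at a standardised effect of 0.45, for both ISI and CALI-9.

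**The concern.** Under 1:1 randomisation the arms have the same expected baseline mean. A model with baseline as a response and a free group main effect does not use that fact. It estimates the chance baseline imbalance and subtracts it in full from the later difference, which is what a change score does. Regression on baseline subtracts only the part that baseline predicts, and so has a smaller variance whenever r is below 1.

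Two comparisons are exposed.

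- **Headache outcomes at 6 months.** The adjusted cross-sectional regression is extended only to phase 2 post-treatment, so the interaction test is the only 6-month analysis given.
- **CALI-9 at phase 2 post-treatment.** Both the adjusted regression and the interaction test address the same hypothesis. The adjusted regression comes first only by analogy with phase 1, while the outcome definition (change to all three assessments) points towards the longitudinal model. The two tests differ in efficiency and can disagree, so the order should be explicit.

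**Working it through.** **Inputs.** From Sample size {14}: 77 per group, 80% power, d = 0.45, 15% attrition, 180 enrolled, 154 final. From Trial design {8}: "The patient allocation ratio is 1:1". Assumed: two-sided alpha 0.05 (not stated; one-sided 0.05 would need only 62 per group), equal SD of 1 at each visit, and r from 0.3 to 0.7 (none is given).

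**The plan's own figure.** n = 2(1.960 + 0.842)²/0.45² = 77.5, so 78 per group; power at 77 is 79.7% (79.2% by the exact t calculation). For attrition, 154/0.85 = 181.2 and 180 × 0.85 = 153. The stated figures are reproduced to within rounding.

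**Variances per participant.**

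- Change score (the interaction contrast): 2(1 − r)
- Baseline-adjusted: 1 − r²
- Ratio, adjusted to change: (1 − r²)/[2(1 − r)] = (1 + r)/2

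**Power** at 77 per arm, with d = 0.45 on the outcome SD, using SE = √(2 × variance/77) and a noncentral t:

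| r (assumed) | Change variance | Adjusted variance | Ratio | Power, interaction | Power, adjusted |
|---|---|---|---|---|---|
| 0.3 | 1.40 | 0.91 | 0.65 | 65% | 83% |
| 0.5 | 1.00 | 0.75 | 0.75 | 79% | 89% |
| 0.7 | 0.60 | 0.51 | 0.85 | 95% | 97% |

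Example at r = 0.5: the SEs are √(2 × 1.00/77) = 0.161 and √(2 × 0.75/77) = 0.140.

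**If d is instead scaled on the SD of change**, the interaction test keeps about 80% power at every r. The adjusted test then has about 93%, 90% and 86% at r = 0.3, 0.5 and 0.7 (normal approximation).

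**Simulation check.** 150 datasets per scenario, 77 per arm, four visits, all correlations 0.5, effect 0.45 SD at each follow-up, random-intercept fit, phase 2 contrast.

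- **Complete data.** The interaction coefficient equalled the raw difference in mean change (largest gap 7 × 10⁻¹⁵). Mean SE was 0.161 for the model as written and 0.139 for both the constrained-baseline model and the adjusted regression. Power was 83%, 89% and 90%.
- **15% dropout.** The match with raw change was approximate (correlation 0.985, largest gap 0.083), but the loss remained: mean SE 0.167 against 0.146 for both alternatives.
- **Agreement.** The interaction test and the adjusted regression gave different significance verdicts in 13% of complete datasets and 10% of those with dropout.
- **Baseline as a covariate.** Adding the baseline value as a main effect to the four-visit model left the interaction estimate unchanged (−0.5817 both ways in a check dataset). Reading the unspecified confounders as including baseline therefore does not recover the precision.

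**The case against.** The strongest reply is that baseline adjustment is already attached to the primary hypotheses, and that a group-by-time model with baseline as a response is conventional, unbiased under randomisation, and tests change from baseline, which is how Outcomes {12} defines the endpoints. That stands for phase 1: ISI has a named, baseline-adjusted primary test. At phase 2 post-treatment it stands only by extension, and it does not reach 6 months.

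The power figures also rest on an r and a scaling of d that the article does not give. At r = 0.5 or above the interaction test has about the planned power even on the outcome-SD scale. That is right, and it limits the point to efficiency.

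Three stronger readings are tempting, and the document supports none of them.

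- **That the primary Wald test targets the baseline difference.** In the four-visit model the group coefficient is the baseline difference. But the sentence on the treatment indicator belongs to the cross-sectional regression and precedes the longitudinal model, for which the plan names the interaction terms instead.
- **That type I error is inflated.** A random-intercept-only model can reject too often if follow-ups correlate more with each other than with baseline. The article says only that mixed effects models will be used. It does not fix that structure, and covariance detail is commonly left to the analysis plan.
- **That the trial is underpowered.** This would need both a low r and d scaled on the outcome SD, and neither is stated.

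**Conclusion.** The point holds as a loss of efficiency, not of validity. As written, the longitudinal interaction test is a change-score comparison for continuous outcomes: exactly so with complete data, approximately with dropout. Baseline adjustment would cut its variance by 35/25/15% at r = 0.3/0.5/0.7. On the outcome-SD scale that is worth about 18, 10 and 2 percentage points of power.

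These sizes assume equal SDs across visits, two-sided alpha 0.05 and the stated 77 per arm, and r is an assumption throughout. The direction does not depend on r, provided that it is below 1 and the SDs are equal.

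The loss affects headache outcomes at 6 months most. It also affects CALI-9 at phase 2 post-treatment, where two tests of one hypothesis are ranked only by implication. It does not affect the primary ISI test, and it does not show the sample size to be wrong. This is a free improvement.

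**What to change.** Replace the longitudinal form with one of two equivalent choices:

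1. **Common baseline mean.** Keep all four visits as responses and drop the group main effect at baseline. Fit time, treatment × time at the three post-baseline visits, and age, sex, race and ethnicity, with a covariance structure that lets the visit correlations differ.
2. **Post-baseline responses only.** Fit group, time and group × time over the three later visits, with baseline and baseline × time as covariates alongside the same demographic covariates.

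Then state that the baseline-adjusted contrast is the primary test for CALI-9, name its time point, and use the same model for the 6-month headache comparison. Label t-tests and unadjusted change scores as supportive. The ISI test needs no change.

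The cost is wording in the analysis section. The data, visits and sample size stay the same, and either model still yields an adjusted between-arm difference at each visit. It should be settled before treatment codes are released for analysis.

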### Interim analyses {21b}

There are no interim analyses planned.

### Methods for additional analyses (e.g., subgroup analyses) {20b}

We will examine the effect of treatment adherence on primary and secondary outcomes. We will create a treatment exposure variable (number of completed treatment modules) and test the significance of coefficients for the time-by-treatment exposure interaction terms.

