### Interventions

#### Explanation for the choice of comparators {6b}

Adolescents assigned to the control condition in treatment phase 1 receive access to a sleep education website (Sleep EDU) that was developed for this study. The education materials are delivered in six treatment cores, designed to be completed once per week over 6 weeks. The program is metered so that adolescents complete one core per week. Parents receive three email messages (one every 2 weeks) with a summary of the information provided in the adolescent program. The education materials do not include any instruction in cognitive or behavioral skills for insomnia. The content was compiled from publicly available educational websites about sleep (e.g., Kids Health, Sleep Foundation, American Academy of Sleep Medicine). The purpose of this comparator condition is to control for time, attention, and Internet usage and to allow masking of treatment allocation. In our prior RCTs using similar online patient education control conditions, youth and parents have shown a high level of engagement and high ratings of treatment credibility [16].

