#### Intervention description {11a}

##### CBT-Insomnia intervention

Adolescents assigned to CBT-I in treatment phase 1 receive access to the Firefly website, an interactive, self-guided intervention that delivers the core components of CBT-I for adolescents. Firefly was adapted from face-to-face CBT-I for adolescents with insomnia and comorbid physical and mental health conditions and Internet-delivered CBT-I for adults [14, 15, 23, 24]. Firefly includes six treatment cores: (1) introduction to the intervention and goal setting, (2) sleep restriction, (3) stimulus control, (4) cognitive skills for sleep, (5) sleep hygiene, and (6) relapse prevention and maintenance. Firefly includes a daily sleep diary which is used to generate tailored recommendations for sleep restriction. Consistent with the core principles of CBT-I, the overarching goal of treatment is to develop a consistent sleep-wake schedule and strengthen the association between bed and sleep by limiting time awake in bed.

Firefly is metered so that adolescents complete one core per week. Each core includes interactive features to deliver skills training including animations, games, quizzes, and vignettes of peers. At the end of each core, adolescents review their knowledge with brief quizzes and then receive an assignment corresponding with the skills taught in the core (e.g., follow their recommended sleep schedule for sleep restriction, set up a nesting place for stimulus control). Youth are asked to practice the skills in each assignment and complete their daily sleep diary for 7 days, until the next core is released. To support engagement, automated emails are sent when it is time to complete a new treatment core, to enter sleep diaries, and to encourage the completion of homework assignments. See Fig. 3 for screenshots of the Firefly program.

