##### CBT-Pain intervention

Treatment phase 2 begins 2–3 weeks after completion of treatment phase 1. In treatment phase 2, all adolescents and parents receive access to WebMAP, an established Internet-delivered CBT-Pain intervention for youth with chronic pain. WebMAP has demonstrated small to moderate treatment effects for improving pain-related disability in multiple clinical trials of youth with chronic pain conditions [16, 17]. WebMAP is guided by cognitive-behavioral, social learning, and family system frameworks [25]. Adolescents and parents access separate versions of the program. The adolescent version of the program includes six treatment cores: (1) pain education and goal setting, (2) cognitive skills for pain management, (3) relaxation methods, (4) coping with pain outside the home, (5) healthy habits, and (6) relapse prevention and maintenance. The parent version of the program also includes six cores: (1) pain education and goal setting, (2) family resilience strategies, (3) operant training, (4) communication skills, (5) modeling and self-care, and (6) relapse prevention and maintenance.

WebMAP is metered so that adolescents and parents complete one core per week. Interactive features include animations, games, quizzes, audio files of relaxation exercises, and video and story vignettes of adolescents and parents coping with pain. At the end of each core, users review their knowledge with brief quizzes and then receive an assignment corresponding with the skills taught in the core (e.g., practice relaxation methods using the audio files). Youth and parents are asked to practice the skills in each assignment for 7 days, until the next core is released. For more details about WebMAP, please see our prior publications [16, 17, 26].

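### The planned adherence analysis reads a self-selected module count as an effect, so it can show a dose-response when the modules do nothing

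*Protocol article*

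**What the plan says.** The protocol's section on additional analyses {20b} gives the aim, "We will examine the effect of treatment adherence on primary and secondary outcomes", and then the method, "We will create a treatment exposure variable (number of completed treatment modules) and test the significance of coefficients for the time-by-treatment exposure interaction terms". It attaches no causal method and no caveat that the result is an association.

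The section on statistical methods {20a} sets the longitudinal model, "All regression models will have the following form: outcome ~ group + time + time × group + confounders", and describes the outcome regressions as adjusted "with a priori identified biological covariates (age, sex), sociodemographic variables (race, ethnicity), and baseline outcome values".

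Three programs supply modules that could be counted:

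- Sleep EDU, the phase 1 control {6b}: "The education materials are delivered in six treatment cores, designed to be completed once per week over 6 weeks". On its content: "The education materials do not include any instruction in cognitive or behavioral skills for insomnia".
- Firefly, the phase 1 CBT-I program {11a}: "Firefly includes six treatment cores".
- WebMAP, given to both arms in phase 2 {11a}: "The adolescent version of the program includes six treatment cores".

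The section on adherence strategies {11c} says that module completion is tracked by web analytics, so the count records what each adolescent chose to do.

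**The concern.** Arm is randomized; the number of modules completed is not. An adolescent who is motivated, or whose family is supportive, may finish more modules and may also improve more for reasons unrelated to their content. Nothing in the named covariates measures either trait. Baseline outcome covers initial severity only in part. The time-by-exposure coefficient then mixes any real benefit of modules with the prognosis of the people who complete them.

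There is a separate problem of dose. The interaction as stated contains no arm. Unless one is added, or the arms are fitted separately, a Sleep EDU core without insomnia skills and a Firefly core share one slope.

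The analysis covers every primary and secondary outcome. A finding of more modules, more benefit could be taken as dose-response support for programs that the Discussion presents as suited to wide dissemination.

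**Working it through.** **Sample size used.** The adherence analysis has no figure of its own. The sample size section {14} gives 77 per group, hence 154. At an assumed two-sided 5% level, 2 × (1.96 + 0.842)² / 0.45² = 77.5, so 78 per group against 77 stated; 180 × 0.85 = 153 against 154. The plan's figures reproduce closely and serve here only to fix N = 154.

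**Null simulation.** 3,000 trials, 1:1, with no effect of modules or arm on the outcome.

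- Motivation M is standard normal and unmeasured.
- Latent completion L = r1·M + √(1 − r1²)·e. Modules = 4.5 + 1.5·L, rounded and limited to 0–6.
- Change from baseline, in SD units with negative as improvement, = −r2·M + √(1 − r2²)·e′.
- The correlation between latent engagement and improvement is therefore r1 × r2.

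Change is regressed on modules. For a single follow-up, the module slope plays the role of the time-by-exposure term, and an arm term plays the role of time × group. The values of r1, r2, 4.5 and 1.5 are assumptions; the documents give none of them.

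Share of trials with p < 0.05:

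| r1 | r2 | r1 × r2 | Modules only | With arm term | CBT-I arm only | Randomized comparison |
|---|---|---|---|---|---|---|
| 0 | 0 | 0 | 4.3% | 4.4% | 4.5% | 4.5% |
| 0.3 | 0.3 | 0.09 | 17.8% | 17.4% | 11.3% | 5.4% |
| 0.5 | 0.3 | 0.15 | 42.4% | 41.8% | 24.1% | 4.4% |
| 0.5 | 0.5 | 0.25 | 84.2% | 84.1% | 55.8% | 5.1% |

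The mean spurious slope in the last three rows is about −0.06, −0.11 and −0.18 SD per module. It is practically the same with modules only, with an arm term, and within the CBT-I arm. The within-arm rejection rate is lower only because N is halved.

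**Cross-check.** With correlation r, the Fisher approximation to the rejection rate is Φ(√(N − 3)·atanh(r) − 1.96), where √151 = 12.29.

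- r = 0.1: 12.29 × 0.1003 = 1.23, giving about 23%.
- r = 0.2: 12.29 × 0.2027 = 2.49, giving about 70%.
- r = 0.3: 12.29 × 0.3095 = 3.80, giving about 97%.

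Simulating with the engagement–change correlation set directly at 0.1, 0.2 and 0.3 gives 21%, 68% and 95%. The small shortfall fits the rounding and capping of the count.

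**Scale.** If CBT-I worked exactly at the design effect of 0.45 SD, the benefit per core would be 0.45/6 = 0.075 SD with all six cores completed, 0.45/4.5 = 0.10 with an assumed average of 4.5, and 0.45/3 = 0.15 with an assumed average of three. The comparison is rough, because outcome SD and change SD differ, but the spurious slopes are of the same order as a real effect.

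**Arm in the model.** Adding time × exposure to the general form in {20a} leaves one exposure slope common to both arms. Group and time × group shift the arm means; they do not let the slope differ. Only an arm-by-exposure-by-time term or separate fits would do that.

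**The case against.** A reader might infer that the protocol pools the arms and that pooling creates the bias. Neither is supported. Section {20b} does not say how arm enters, and the general form in {20a} suggests that group terms stay. The calculation puts the cause in self-selection: the spurious slope is the same with an arm term or within one arm. The shared slope is a separate matter. Which modules are counted is a detail that an article may leave to the full protocol, and is not held against it here.

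A reader might also infer that a false dose-response will be reported. That is too certain. The size depends on correlations that the documents do not give, and completion could track greater severity and push the other way.

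Nor do the documents show that low completers will lack outcomes. The retention section {18b} invites everyone to follow-up, including those who do not finish the intervention, and {20c} adds multiple imputation if missing data are substantial.

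This is an additional analysis. The primary analyses are intent-to-treat {20c}, and the primary hypotheses are tested on the treatment indicator {20a}; the last column of the table stays near 5%. That stands, and it limits the weight of the point.

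Finally, an instrument has limits. Both arms receive WebMAP, so arm cannot be an instrument for WebMAP exposure. In phase 1, Firefly's sleep diary, automated emails and parent emails may act without core completion. With arm as the only instrument, the estimate essentially rescales the intent-to-treat contrast. These objections stand and shape the fix, but they do not make the planned coefficient an effect of adherence.

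**Conclusion.** The point holds. The protocol names the exposure and the test and calls the target an effect, so this is more than an omitted detail. With no true effect and N = 154, an engagement–change correlation of about 0.1 gives roughly 20% false positives, four times the nominal 5%, and 0.2 gives roughly 70%. Group terms do not change this. The rates rest on assumed correlations of unknown size and direction, and on covariates that do not stand in for motivation or family support.

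The randomized comparisons, and so the trial's main conclusions, are untouched. This is a cheap improvement to an additional analysis.

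**What to change.** - **Phase 1 outcomes.** Estimate the effect of Firefly exposure with randomized arm as the instrument: two-stage least squares on Firefly cores completed (zero by design under Sleep EDU), or a complier average causal effect at a pre-stated number of cores, adjusted for the planned covariates. State the exclusion restriction, and note that the diary and emails may act without core completion. If a threshold is used, add that adolescents below it are assumed to gain nothing from the cores they did complete.
- **WebMAP exposure in phase 2 and every other module-count analysis.** Report the association by arm and by program, labelled descriptive, and do not interpret it as an effect of adherence. Splitting by arm keeps Sleep EDU and Firefly cores apart; it does not remove the self-selection bias, so the label is still needed.
- **Wording of {20b}.** Replace the language of effect with association wherever the module count is the predictor.

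The cost is a few sentences and a little programming. The price is wider intervals than the module-count regression gives, and an assumption that the data cannot test.
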